***Data Collection Tools/ Measures:***

Diabetes Self Efficacy Scale (DSES) is an 8-item with a scale ranging from 1 (not at all confident) to 10 (totally confident). The score for the scale is the mean of eight items where higher number indicated higher self-efficacy (Ritter et al., 2016). This scale is found to have good internal consistency and test- retest validity (Kerari, 2023; Mankan et al., 2017) and have been modified and used in Nepalese context (Dwa & Panthee, 2021).

Multidimensional Scale of Perceived Social Support is a 12-item, 7-point Likert scale (1 as very strongly disagree to 7 as very strongly agree) to assess perceived support from family,friends and significant other (Zimet et al., 1988). Nepalese version of this scale is found to have good construct validity and reliability (Tonsing et al., 2012).

Diabetes Distress Scale consists of 17 questions in total: Emotional burden (5 questions), Physician related distress (4 questions), Regimen related distress (5 questions) and Interpersonal distress (3 questions). Responses for the question ranges from 1 (slight problem) to 6 (very serious problem). Mean is calculated for each subscale. This scale is found to be valid and reliable tool to assess distress among people with type 2 diabetes in context similar to Nepal (Akter et al., 2022).

WHOQOL- BREF consists of 26 items across four domains: physical, psychological, social and environment including the questions on overall quality of life and general health. The score ranges from 1 to 5 on a response scale. Higher scores denote higher quality of life (WHO, 1998). This tool is found have good internal consistency and validity in assessing the quality of life of people across different cultures (Almarabheh et al., 2023; Kalfoss et al., 2021; Sreedevi et al., 2016) including Nepal (Joshi et al., 2023).We will use Nepali version of WHOQOL-BREF.

Revised scale of Summary of Diabetes Self Care Activities measure consists of core set of 11 items from Summary of Diabetes Self Care Activities measure and additional 14 questions (Toobert et al., 2000). It is found to be valid and reliable tool for assessing self- care behavior among adults with diabetes (Jalaludin et al., 2012).

Economic evaluation: An economic evaluation will be done of the intervention considering the following aspects: a. Cost (Resource Measurement) The study will measure both direct and indirect costs, including medical expenses (e.g., medication, hospital charges) and non-medical costs (e.g., travel, lost income). These costs will be valued based on actual patient payments and market rates, excluding non-monetized factors like leisure time. b. Cost of the mHealth Intervention Costs associated with the intervention will be calculated using project data, converting monetary values from Nepalese currency to Great Britain Pounds (GBP) at the appropriate exchange rate. Unit costs will be based on actual records. c. User’s Perspective Cost Measurement Out-of-pocket expenses, including medical and non-medical costs, will be collected from participants retrospectively at baseline and prospectively during the study. Participants will record expenses in forms and diaries, which will be used during follow-up data collection. d. Effects Measurement (Health-related Outcomes) The study will assess health outcomes such as HbA1c levels, self-care management, and quality of life using the EuroQol-5 Dimension (EQ-5D) tool. This will help measure Quality-Adjusted Life Years (QALYs), using the Indian EQ-5D value set due to the cultural similarities between Nepal and India. e. Incremental Cost-Effectiveness Ratio (ICER) ICER will measure the economic value of the intervention by comparing the incremental costs and health outcomes (e.g., QALYs gained, HbA1c reduction) between the intervention and control groups.

Acceptability of the intervention will be measured through “Yes” or “No” questions on usefulness, appropriateness, sharing, learning and support in diabetes management and behavior change (Dobson et al., 2016).

Physical measurements

Blood pressure, height and weight will be measured following standard guideline for measurement from WHO STEPS Survey, Nepal (Dhimal M et al., 2019).

Height: Height will be measured using a portable stature meter and values will be recorded in centimetres. We will ensure that the participants removed footwear or any accessories on the head and stands on a flat surface with their feet 10 cm apart and heels against the wall with knees straight.

Weight: Weight is measured using a portable digital seca weighing scale and values will be recorded in kilograms. We will ensure that the participant is on light clothing and without footwear.

Blood pressure: We will use an Omron digital automatic blood pressure monitor with universal sized cuffs to measure blood pressure. Three readings of blood pressure will be taken with an interval of 3 minutes each between the readings after having asked the participant to sit and rest for 15 minutes.

Blood collection There are no specific conditions (fasting, special diets) required for patient. A trained lab person will collect the blood sample using aseptic technique. Laboratory technician and laboratory technologist are responsible for conducting this test and the test will be performed in a laboratory of Dhulikhel hospital. HbA1c test will be performed following standard protocols of the laboratory.

***Pretesting***

A pretesting of the questionnaire will be done among people with type 2 diabetes. In addition, the content developed will be pre-tested among participants similar to target group to improve on content validity.

***Validity and Reliability of tool***

Diabetes Self Efficacy Scale (DSES) is an 8-item with a scale ranging from 1 (not at all confident) to 10 (totally confident). The score for the scale is the mean of eight items where higher number indicated higher self-efficacy (Ritter et al., 2016). This scale is found to have good internal consistency and test- retest validity (Kerari, 2023; Mankan et al., 2017) and have been modified and used in Nepalese context (Dwa & Panthee, 2021). Multidimensional Scale of Perceived Social Support is a 12-item, 7-point Likert scale (1 as very strongly disagree to 7 as very strongly agree) to assess perceived support from family, friends and significant other (Zimet et al., 1988). Nepalese version of this scale is found to have good construct validity and reliability (Tonsing et al., 2012). Diabetes Distress Scale consists of 17 questions in total: Emotional burden (5 questions), Physician related distress (4 questions), Regimen related distress (5 questions) and Interpersonal distress (3 questions). Responses for the question ranges from 1 (slight problem) to 6 (very serious problem). Mean is calculated for each subscale. This scale is found to be valid and reliable tool to assess distress among people with type 2 diabetes in context similar to Nepal (Akter et al., 2022). WHOQOL- BREF consists of 26 items across four domains: physical, psychological, social and environment including the questions on overall quality of life and general health. The score ranges from 1 to 5 on a response scale. Higher scores denote higher quality of life (WHO, 1998). This tool is found have good internal consistency and validity in assessing the quality of life of people across different cultures (Almarabheh et al., 2023; Kalfoss et al., 2021; Sreedevi et al., 2016) including Nepal (Joshi et al., 2023). We will use Nepali version of WHOQOL-BREF. Revised scale of Summary of Diabetes Self Care Activities measure consists of core set of 11 items from Summary of Diabetes Self Care Activities measure and additional 14 questions (Toobert et al., 2000). It is found to be valid and reliable tool for assessing self- care behavior among adults with diabetes (Jalaludin et al., 2012). Blood pressure, height and weight will be measured following standard guideline for measurement from WHO STEPS Survey, Nepal (Dhimal M et al., 2019). HbA1c test will be performed in a laboratory affiliated to National Public Health Laboratory, Nepal. HbA1c test will be performed following standard protocols of the assigned laboratory.

Furthermore, to determine the validity of the developed intervention (text message), expert rating on the content will be used where experts (5-6) will be asked to rate each message on a scale of 1 to 4 where, 1=not relevant, 2=somewhat relevant, 3=quite relevant and 4=highly relevant. A content validity index will be calculated.

***Plan for specimen/data management:***

Participants will be assigned unique identifiers or codes to ensure anonymity. No personal identifiers will be revealed beyond the researcher(s) managing the data and it will not be used while reporting the results or sharing data. Confidentiality of the data will be protected in accordance with the requirements of the General Data Protection Regulation (GDPR) and Data Protection Act 2018, University of Huddersfield. Data will be kept confidentially in accordance with the general data requirements of the General Data Protection Regulation (GDPR) and Data Protection Act 2018. All files from data collection will be securely stored in locked cabinet. Electronic data will be initially stored in a password protected laptop and then transferred to one drive at earliest possibility to prevent loss of data. Only limited people directly involved in the study will have access to data. Data will be stored for a period of 10 years and then be safely destroyed. Hard copies having personal identifiers will be kept until entries of data and then will be securely destroyed. Other research related documents such as consent form will be scanned and securely destroyed.

***Plan for data analysis:***

Quantitative: Data will be managed using SPSS version 20.0. Initially, the demographic and baseline characteristics will be reported using descriptive statistics as frequencies and percentages, mean or median and standard deviation as appropriate. Initially, information collected at different intervals on primary and secondary outcomes will be reported through descriptive summary and comparison will be done using chi-square test for categorical and independent sample t-test for continuous data. The estimated mean difference between and within groups will be calculated along 95% confidence intervals with and statistical significance set at p<0.05. Cost effective analysis will be performed using an incremental cost-effectiveness ratio (ICER) that will measure the economic value of the intervention by comparing the incremental costs and health outcomes (e.g., QALYs gained, HbA1c reduction) between the intervention and control groups. Qualitative: Interviews will be audio recorded and then transcription in Nepali and subsequently translated to English for analysis. The qualitative data will be analysed using a thematic analysis approach (19). Interview transcripts will be read and re-read, formally coded and categorized and sub-categorized into emerging thematic areas. The results will be explained under the thematic areas and will be supported by verbatim quotes.

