#### Summary of the proposed research protocol (within 200 words)

The overall burden of diabetes is rising, especially in low and middle-income countries such as Nepal. In Nepal, access to diabetes care varies by socio-economic and geographical factors, posing significant challenges to prevention and control. Self-management plays a crucial role in the prevention and control of diabetes. Mobile health (mHealth) technology is increasingly popular for managing chronic diseases, demonstrating its feasibility, acceptability, and effectiveness in enhancing health outcomes and encouraging behavior change. However, its impact on improving self-management among people with type 2 diabetes in Nepal remains unexplored. This randomised controlled trial aims to evaluate a 6-month text based mhealth intervention that support self- management among people with type 2 diabetes in Nepal. The primary outcome includes change in HbA1c at 6 months. Secondary outcomes include behaviour change for diabetes self-management activities, self-efficacy, perceived support, diabetes related stress, quality of life and acceptability of the intervention acceptability. In addition, an economic evaluation will be conducted using a patient perspective. Primary and secondary outcomes will be summarized descriptively, and comparisons will be made using chi-square tests for categorical data and independent sample t-tests for continuous data using SPSS. A cost-effectiveness analysis will be conducted using the incremental cost-effectiveness ratio (ICER).

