***Specific objective(s):***

1. To identify the barriers and facilitators in adoption of text based mhealth intervention in self-management of type 2 diabetes
2. To explore the perspective of service providers and end users on use of text based mhealth for self-management of type 2 diabetes
3. To develop a theory based contextual text based mhealth intervention that support self-management in people with type 2 diabetes
4. To determine the effectiveness, cost-effectiveness and acceptability of text based mhealth intervention in supporting self-management in people with type 2 diabetes

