7. Self-care activities: Revised scale of Summary of Diabetes Self Care Activities measure consists of core set of 11 items from Summary of Diabetes Self Care Activities measure and additional 14 questions ([Toobert et al., 2000](#_ENREF_52)). It is found to be valid and reliable tool for assessing self-care behavior among adults with diabetes ([Jalaludin et al., 2012](#_ENREF_24)).
8. Economic evaluation: Economic evaluation of the intervention will be done using the cost information obtained at baseline and follow up (after 6 month) including the cost of development and delivery of mhealth intervention and Quality-adjusted Life Years (QALYs).
9. Acceptability of intervention: Acceptability of the intervention will be measured through “Yes” or “No” questions on usefulness, appropriateness, sharing, learning and support in diabetes management and behavior change ([Dobson et al., 2016](#_ENREF_11)).

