A simple randomization technique ([Kang et al., 2008](#_ENREF_29)) will be used to assign participants to either intervention or control group on 1:1 basis. Concealment of allocation will be done using Sequentially numbered, opaque, sealed envelope (SNOSE) technique ([Sil et al., 2019](#_ENREF_46)).An open-source random number sequence generator (random.org) will be used to generate random numbers in two columns (77 each) from 1 to 154 indicating column one for intervention group and column two for control group ([random.org](#_ENREF_41)). The generated numbers in column one and column two will be kept in sequential order in two separate opaque sealed envelopes with a number labelled on outside. The lead researcher will generate the random number and prepare the envelopes while the research assistant will assign the participants to intervention or control group accordingly. A face to face interview will be conducted with people with type 2 diabetes using a structured questionnaire which includes questions related to self-efficacy, perceived support, stress, quality of life, self-care behavior and cost (disease related and development and delivery of intervention) including questions on acceptability of the intervention at follow up. Data will be collected at baseline and 6 months after the intervention.

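### The ICER is the only economic measure named, and its cost-per-QALY form may be unstable at about 61 per arm; net monetary benefit and separate increments would be sounder

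*Protocol*

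**What the plan says.** Three places in the protocol name the economic measure, and each names the ICER alone.

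- The Summary says: "A cost-effectiveness analysis will be conducted using the incremental cost-effectiveness ratio (ICER").
- Data Collection Tools/ Measures, Economic evaluation item e, gives the ICER the task of measuring economic value.
- Plan for data analysis repeats this: "Cost effective analysis will be performed using an incremental cost-effectiveness ratio (ICER) that will measure the economic value of the intervention", which it does by "comparing the incremental costs and health outcomes (e.g., QALYs gained, HbA1c reduction) between the intervention and control groups".

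Two denominators are thus offered as examples: QALYs and HbA1c reduction.

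On QALYs, Economic evaluation item d names EQ-5D and adds: "This will help measure Quality-Adjusted Life Years (QALYs), using the Indian EQ-5D value set". On timing, Data Collection Procedure says: "Data will be collected at baseline and 6 months after the intervention". Study Variables item 8 gives the same two time points for costs.

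Sample size determination uses HbA1c only: 122 evaluable, 153 after 20% attrition, 154 randomised. The 95% CIs in Plan for data analysis are for mean differences between and within groups.

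Specific objective 4 reads: "To determine the effectiveness, cost-effectiveness and acceptability of text based mhealth intervention in supporting self-management in people with type 2 diabetes".

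**The concern.** An ICER is a ratio of two estimated differences. It behaves well only when the denominator is clearly away from zero. Otherwise there are two difficulties.

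1. When the 95% CI of the effect difference includes zero, a Fieller 95% interval for the ratio is unbounded.
2. A negative ratio shown alone does not separate an intervention that is cheaper and better from one that is dearer and worse.

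The CIs planned for mean differences do not supply an interval for a ratio. If the QALY difference is small against its standard error, the cost-per-QALY figure could have a sign and size that are mostly noise. A reader of the results would have little else on which to judge the cost-effectiveness part of objective 4.

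**Working it through.** **1. The plan's own figure.** From Sample size determination, the HbA1c difference is 0.86 − 0.18 = 0.68 and the pooled SD is √((1.08² + 1.53²)/2) = 1.324. With two-sided 5% (sidedness is not stated) and 80% power, the normal formula gives 2(1.96 + 0.84)² × 1.324² / 0.68² ≈ 59.5, so 60 per arm. The t-based calculation gives 61 per arm (power 80.3%), which is 122. Then 122/0.80 = 152.5, so 153, made even at 154. The figure reproduces, and about 61 per arm are expected to be evaluable.

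**2. QALYs from two visits.** EQ-5D is taken to be collected at the two stated data-collection times. By the trapezoid rule over half a year, QALY = 0.5 × (u0 + u6)/2 = 0.25(u0 + u6). With balanced baselines, the QALY difference is 0.25 × the six-month utility difference.

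**3. Assumptions not in the protocol.** Utility gain g = 0.03, SD 0.15 to 0.20 at each visit, baseline–follow-up correlation r = 0.5. The QALY difference is then 0.25 × 0.03 = 0.0075.

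**4. Standard errors with n = 61 per arm.**

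- Unadjusted: SE = √(0.0625 × 2 × SD² × (1 + r) × 2/n). For SD 0.15 this is √(0.004219 × 2/61) = 0.0118; for SD 0.20 it is √(0.0075 × 2/61) = 0.0157.
- Baseline-adjusted: SE = 0.25 × SD × √(1 − r²) × √(2/n). For SD 0.15 this is 0.25 × 0.15 × 0.866 × 0.181 = 0.0059; for SD 0.20 it is 0.0078.

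With z = 0.0075/SE, P(estimate below 0) = Φ(−z), and P(95% CI includes 0) = Φ(1.96 − z) − Φ(−1.96 − z).

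| SD | Analysis | SE | z | Estimate below 0 | CI includes 0 |
|---|---|---|---|---|---|
| 0.15 | unadjusted | 0.0118 | 0.64 | 26% | 90% |
| 0.20 | unadjusted | 0.0157 | 0.48 | 32% | 92% |
| 0.15 | adjusted | 0.0059 | 1.28 | 10% | 75% |
| 0.20 | adjusted | 0.0078 | 0.96 | 17% | 84% |

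The factor of 0.25 enters both the difference and its SE, so it cancels in z. It makes the QALY gain small in absolute terms. The instability itself comes from the utility gain being small against its spread at this sample size.

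**5. Range of assumptions.** Over SD 0.10 to 0.25, gain 0.02 to 0.05 and r 0.5 to 0.7, the unadjusted chance of a below-zero estimate runs from about 6% to 40%. At the favourable end (gain 0.05, SD 0.10, r = 0.5), the CI includes zero in 64% unadjusted but only 11% adjusted, with a below-zero chance under 1% adjusted.

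**6. The HbA1c denominator.** On the protocol's inputs, SE = √((1.08² + 1.53²)/61) = 0.240 and z = 0.68/0.240 = 2.84. The chance of a wrong-signed denominator is about 0.2%. Its CI would include zero in about 20% of trials, which is the type II error the design already accepts.

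**The case against.** The case on the other side has several parts, and most of them limit the point.

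- **An ICER is a standard summary, and its uncertainty methods usually sit in an analysis plan that is not shown.** This stands. The absence of a threshold, bootstrap or acceptability curve is not a finding here. What remains is that the protocol itself fixes the measure, in three places, as the ratio alone.
- **A reader might infer that cost-effectiveness will be decided by the ICER.** The text does not say so. It calls the ICER a measure and states no threshold or decision rule.
- **A reader might infer that the QALY difference has been shown to be indistinguishable from zero.** It has not. The gain, SD and correlation are assumptions, and the problem largely disappears with a gain of 0.05, an SD of 0.10 and baseline adjustment. Against this, the only comparisons the protocol names are chi-square and independent-sample t-tests, and it mentions no baseline adjustment, so the unadjusted figures are closer to the plan as written.
- **The trial is powered for the other denominator.** This stands. The instability argument barely touches cost per unit of HbA1c.
- **A reader might infer that objective 4 cannot be answered.** That is too broad. Effectiveness and acceptability do not depend on the ICER.
- **A negative ratio is ambiguous only if its components are hidden, and a Fieller interval is unbounded only when the denominator is not significantly different from zero.** Both are correct. They support showing the components beside the ratio.

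**Conclusion.** The point holds in a limited form. The protocol names the ICER as its only measure of economic value, and in its cost-per-QALY form that ratio may well be unstable at the planned size. Under a gain of 0.03, SD 0.15 to 0.20 and correlation 0.5, the chance of a wrong-signed QALY difference is 26–32% unadjusted and 10–17% adjusted. The chance that its CI includes zero is 90–92% and 75–84% respectively. These figures rest on assumed utility inputs and on EQ-5D being taken at both visits; larger gains with smaller SDs reduce them. The HbA1c-based ICER and the effectiveness and acceptability parts of objective 4 are not materially affected. This is an inexpensive improvement to a secondary analysis and does not bear on the validity of the primary comparison.

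**What to change.** In Data Collection Tools/ Measures, Economic evaluation item e, and in Plan for data analysis:

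1. Report incremental cost and incremental QALYs separately, each with a 95% CI.
2. Base the cost-per-QALY conclusion on incremental net monetary benefit (threshold × incremental QALYs − incremental cost) over a stated range of thresholds. Use one currency for thresholds and costs; Economic evaluation item b converts intervention costs to GBP, so this must be settled.
3. Give net benefit a bootstrap CI that resamples participants within arm, keeping each person's cost and effect together.
4. Keep the ICERs, including cost per unit of HbA1c, as descriptive summaries shown beside their two components. Their reporting should not depend on statistical significance.

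The cost is revised wording and a short program, with no new data. The downside is slightly more analysis work and an economic conclusion that looks less certain than a single ratio.
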